**Overdose of the investigational drug**

Overdose events (exceeding the protocol-prescribed dose, including overdose) shall be recorded in the eCRF. Any other AE/SAE associated with overdose must be followed up as any other AE/SAE. Events are reported as AEs/SAEs (such as a suicide attempt) only if they are accompanied by clinical signs and symptoms or if the overdose itself is an AE/SAE.

**Safety signal detection**

Selected data from this study will be reviewed periodically to detect any safety concerns related to investigational drug as early as possible so that the Investigator, clinical study subjects, Certificate Authority (CA), and IRB/IEC can be notified appropriately and as early as possible.

The study doctor or medically qualified designee/equivalent personnel will perform ongoing SAE review and ongoing SAE consistency verification in conjunction with the PV representative of Gan & Lee Pharmaceuticals/CRO.

Based on the development stage of the investigational drug and the accumulated experience, other safety assessment measures (e.g.: AEs, vital signs, laboratory or ECG findings) may be determined by medically qualified personnel of Gan & Lee Pharmaceuticals/CRO, and the data will be reviewed periodically during the study.

---

## **8. Study Management and Administration**

### **8.1 Protocol compliance**

Deviations from the protocol, principles of ICH GCP, or applicable regulations are considered “protocol deviations”. The investigator and all personnel involved in the study should carefully read and strictly follow the protocol. The investigator should not deviate from the protocol. Except in case of emergency, no changes or modifications to the protocol may be made during the execution without the consent of Gan & Lee Pharmaceuticals Co., Ltd. If changes or modifications are required, they must be made in accordance with the specified procedures, and the Ethics Committee (IRB/IEC) must be notified of any change or amendment that may increase the risk of the subject and/or have a negative impact on the rights of the subject and the efficacy of the study, and the written consent of the IRB/IEC must be obtained.

However, standard medical care (prophylactic, diagnostic, and therapeutic procedures) remains the responsibility of the subject’s attending physician (the investigator) in order to protect the health and safety of subjects from any immediate risk. If, in the opinion of the investigator or the qualified professional (associate investigator) authorized by the investigator, the safety of the subject would be jeopardized, any necessary measure that deviate from the protocol or are not specified in the protocol may be taken. In these cases, such measures should be taken immediately without prior notification to regulatory authorities, IEC (Independent Ethics Committee)/IRB (Institutional Review Board), and the sponsor.

Protocol deviations caused by emergencies, accidents, or errors must be reported to the sponsor by the investigator or the designated personnel within 24 hours to facilitate an early decision on whether the subject should be withdrawn from the study.

Any protocol deviations should be documented in detail.

### **8.2 Monitoring**

A risk-based approach is used for quality management of the study. Quality management of the study is initiated by assessing the data and procedures critical to subject protection and the reliability of results, as well as identifying and assessing associated risks. The integrated quality and risk management plan documents the rationale and strategy for risk management during the conduct of the trial, including monitoring methods, supplier management, and other processes that focus on the highest risk areas.

---

Ongoing risk review and assessment may lead to adjustments to trial implementation, trial design, or monitoring methods.

This study is monitored by Gan & Lee Pharmaceuticals (or designee) for compliance with the sponsor's SOP for monitoring, ICH-GCP guidelines, and applicable regulatory requirements, and to ensure appropriateness of initiation, implementation and termination of the study. Gan & Lee Pharmaceuticals may entrust the study monitoring to CRO or contract CRA.

The investigator and the personnel shall cooperate with Gan & Lee Pharmaceuticals (or designee) and may answer questions sufficiently and provide any missing information during monitoring visits. The investigator/institution allows direct access to source data/documents for study-related monitoring, audits, IRB/IEC reviews, and regulatory inspections.

The investigator allows Gan & Lee Pharmaceuticals (or designee) to periodically review all eCRFs and corresponding source documents (e.g., hospital and laboratory records for each study participant). Monitoring visits provide an opportunity for Gan & Lee Pharmaceuticals (or designee) to evaluate the study progress, verify the accuracy and completeness of the eCRFs, ensure the realization of all protocol requirements, relevant legal requirements, and investigator obligations, and resolve inconsistencies in the study records.

### **8.2.1 Definition of source data**

In accordance with regulatory requirements, the investigator shall prepare and keep adequate and accurate source documents and study records, including all observations and other study data relevant to each study patient. Source data and reported data should follow the "Attributable, Legible, Contemporaneous, Original and Accurate (ALCOA)" principle and should be attributable, legible, contemporaneous, original and accurate. Data changes should be traceable (audit trail).

All source documents must be accurate, legible, permanent, and auditable. Permanent record modes (in ink, printing, CD-ROM) are required. Data are not allowed to be altered with correction fluid or temporary sticky note (e.g., removable self-stick note). Photocopies and/or printouts of the CRF cannot be used as qualified source documents. The source documents are the originals of the raw data first recorded. Such documents include hospital/outpatient/general practitioner records, charts, logs, X-rays, laboratory results, printouts, pharmacy records, nursing records, ECGs or other printouts, completed scales or quality of life questionnaires, etc. Source documents should be kept in a secure site with

restricted access. Original laboratory test results and other test reports are considered source documents and should be stored with the subject's study information.

Printouts of the source documents generated by the computer and saved electronically must be provided for review by the CRA (e.g., ECG reports). The printed copies should be signed and dated by the investigator and kept permanently in the source documents of the subject. The investigator shall simplify the monitoring process and check the printouts with the data stored in the computer to ensure that all data are consistent and correct.

Electronic data records (e.g., continuous glucose monitoring records, if applicable) must be saved and stored as directed by Gan & Lee Pharmaceuticals (or designee).

### **8.2.2 Source data verification**

Source data verification ensures the accuracy and reliability of the study data.

During monitoring visits, the accuracy, integrity, and traceability of the reported data are reviewed against the source documents (e.g., subject documents, records for automatic instrument, tracings, radiographs, records for laboratory tests). All data reported in the eCRF should be supported by the source documents, unless otherwise specified in Section 8.2.1.

## **8.3 Data processing**

### **8.3.1 Case report form completion**

An electronic data capture (EDC) system is used for this study.

The investigator is responsible for timely reporting of accurate, complete and clear data in the eCRF and all specified reports. Justification is required for any change or correction made after saving of eCRF. Corrections made after review and approval by the investigator (via password/electronic signature) are reapproved by the investigator. The investigator should maintain a list of personnel authorized to enter data into the eCRF.

The data on the eCRF must be consistent with the source data. The inconsistencies must be explained.

The current medical history of the subject may not be sufficient to confirm his/her eligibility for this study. So the investigator may need to ask for evidence of past medical history and any diagnostic tests. In such case, the investigator must make at least one attempt to retrieve the previous medical records and document it. In case of failure, oral medical history provided by the patient may be accepted (if applicable). The investigator shall determine the subject's eligibility for this study based on all available information and document it in the source documents.

---

If the subject does not comply with the protocol, any corrective actions (e.g., retraining) must be documented in the subject file.

For eCRFs, data must be derived from source documents such as:

- Subject identification: Sex, year of birth (according to local laws and regulations)
- Participation of the subject in the study (drug, study protocol number, patient ID, date of informed consent of the patient)
- Date of visit of the subject
- Medical history (including trial indication and concomitant diseases, if applicable)
- AE (onset date (mandatory) and end date (if applicable))
- SAE (onset date (mandatory) and end date (if applicable))
- Concomitant therapy (start date, changes)
- Originals or copies of laboratory results and other imaging or test results, and appropriately documented medical evaluations (in validated electronic format, if applicable)
- Trial completion of the subject (end date; reasons for early termination should be recorded).
- Evidence that the study participant meets all inclusion criteria and none of the exclusion criteria must be documented in source data (e.g. medical records) before he/she is assigned to the clinical study. Lack of documentation to support inclusion/exclusion criteria (whether medical records or verbal record feedback of the patient, or protocol-specified examinations) may result in disqualification of the subject from participating in the clinical study.

Refer to the filling guide of eCRF for detailed instructions.

### **8.3.2 Database entry and consistency verification**

It is the primary responsibility of the investigator to ensure that the data reported on the electronic case report form or otherwise are accurate, complete, and timely, and it should be ensured that the data on the electronic case report form are derived from the original data from the subject and an explanation must be given for any differences.

Clinical research associates (CRAs) are responsible for source data verification (SDV), logging on to the EDC at the site of the research center to verify the consistency of the eCRF data with the source data, and can issue a query online at any time if they find a problem. After the data are filled into the EDC database, the system will automatically verify the data according to the system logic verification that has been set up, and system queries will be issued automatically for problematic data. The Data Manager (DM)

manually verifies the data according to the DVP, and sends manual queries to the EDC database for problematic data.

Challenges issued by the CRA SDV & DM Verification should be answered as soon as possible by the investigator or the clinical research coordinator (CRC) designated and trained by the investigator, and the CRAs and DMs confirm their own queries on the basis of the investigator's answers, and if necessary, may reissue the challenge until all data queries have been resolved.

The investigator or CRC can modify the data after verifying the data, the modified data need to fill in the reason for modification on the eCRF and leave an audit trail in the database, and the investigator needs to audit all the final data. After all the data in the database have been verified and cleaned without doubt by CRA and DM, the principal investigator confirms the authenticity and integrity of the data and signs it electronically.

### **8.3.3 Subject screening and enrollment log/subject identification code list**

Screening information and enrollment information of the subject is recorded in the subject screening and enrollment log.

The investigator keeps a subject identification code list. This list is kept by the investigator for accurate identification of each subject.

The subject's consent to participate in the study and enrollment information must be recorded in the his/her medical records. These data should be labeled "For use in this study only". The date on which the subject participates in the study should be indicated.

## **8.4 Study termination**

Gan & Lee Pharmaceuticals reserves the right to suspend or permanently terminate the study in a single site, multiple sites or all sites at any time for reasons including, but not limited to, safety or ethical issues, incorrect or incomplete data recording, noncompliance, or unsatisfactory quality or quantity of patients recruited.

If the study is early terminated or suspended, Gan & Lee Pharmaceuticals (or its representative) will notify the investigator/study sites and regulatory authorities as required by the appropriate regulatory authorities and provide the reasons for termination or suspension of the study. The sponsor or the investigator/study site should also notify the IRB/IEC and explain the reasons for termination or suspension of the study, as required by the appropriate regulatory authorities. In addition, all unused IMP and other materials will be returned at scheduled times according to the study procedures of Gan & Lee Pharmaceuticals.

---

## **8.5 Archiving and data preservation**

Source documents and other important GCP-specified documents (including ISF) must be kept by study sites and the record keepers of IRB/IEC according to the protocol or for a locally required period of validity at the end of the study (whichever is longer). If Gan & Lee Pharmaceuticals requests to extend the retention period of these documents, the retention period and method will be determined after discussion between Gan & Lee Pharmaceuticals and study sites.

Gan & Lee Pharmaceuticals (or designee) is responsible for informing the record holder when these documents will no longer be retained.

Gan & Lee Pharmaceuticals and its CRO must retain the necessary documents in accordance with their SOPs and contracts.

## **8.6 Audit and inspection**

Upon rational notification, the investigators or the head of the research center involved in this study will allow Gan & Lee Pharmaceuticals to enforce study-related audits and allow inspections by domestic and foreign regulatory authorities.

The primary objective of the audits or inspections is to ensure that the rights and health of enrolled subjects are safeguarded, that the enrolled subjects (i.e., subjects who sign the consent and undergo study procedures) are suitable for participation in this study, and that all relevant data for IMP evaluation have been processed and reported in accordance with established arrangements, the study protocol, SOPs for research center and IRB/IEC, ICH GCP, and relevant regulatory requirements.

If an inspection is notified by a regulatory authority, the investigator should promptly notify Gan & Lee Pharmaceuticals (or designee).

At the time of study-related surveillance, audits, IRB/IEC reviews and regulatory inspections, the investigator must provide direct access to eCRFs and all source documents/data (including copies of progress notes, laboratory results and medical examination results), and must be readily available for review by CRA, auditors, and regulatory inspectors (e.g., Medical Products Administration). They can review all eCRFs and ICFs. The accuracy of the data is verified by direct comparison with the source documents described in Section 8.2.1.

The sponsor and its CRO are also monitor compliance with the protocol and GCP.

## **8.7 Good Clinical Practice**

---

For noncompliance with the protocol, ICH-GCP, or requirements of local regulatory authority by the investigator, study sites, their personnel, or designee of the sponsor, Gan & Lee Pharmaceuticals will take timely measures to ensure compliance. Persistent noncompliance may result in termination of study activities at relevant sites.

## **8.8 Biological samples**

Biological samples for this study will be stored in accordance with national laws and regulations. Gan & Lee Pharmaceuticals and its partners can only use biological samples for the purposes stated in the protocol and ICF. Subjects have the right to request the destruction of their biological samples at any time.

Detailed information on collection, processing, storage, and shipment of biological samples are shown in the sample handling manual or corresponding documents.

## 9. Statistics

The statistical methods are described below.

### 9.1 Definition of analysis sets

**Full Analysis Set (FAS):** FAS includes all randomized subjects who received at least one dose of the investigational drug. The data set is the main analysis set of demographic data, baseline indicators, medical history and curative effect.

**Per Protocol Set (PPS):** PPS is a subset of FAS, which includes subjects who met all inclusion criteria, did not meet exclusion criteria, had primary endpoint efficacy indicators and did not have other major protocol deviations. The data set is used for the supportive analysis of efficacy.

**Safety Set (SS):** SS includes all randomized subjects who received at least one dose of investigational drug and had at least one safety evaluation. This data set is used for statistical analysis of safety indicators.

**PK Concentration Set (PKCS):** PKCS includes all randomized subjects who received at least one dose of investigational drug and had at least one measured plasma concentration of the investigational drug available after medication.

**PK Parameter Set (PKPS):** PKPS includes all randomized subjects who received at least one dose of the investigational drug and had at least one valid PK parameter of the investigational drug during the study.

#### Other

All efficacy analyses are performed primarily in FAS. To verify the robustness of the efficacy results, the primary efficacy variable is also analyzed for PPS. Safety analysis is conducted in SS.

All efficacy analyses are based on randomized treatment assignment, Safe analysis based on actual groups. Subjects receiving incorrect treatment are evaluated during a blinded Data Evaluation Meeting (DEM) to assess the potential impact of such cases and any special analytical considerations.

### 9.2 General statistical consideration

Descriptive statistics such as mean, standard deviation (SD), median, lower quartile (Q1), upper quartile (Q3), minimum and maximum for quantitative variables, and counts and percentages for categorical variables are provided. Critical supporting data are provided in data listings. Unless otherwise stated, all statistical tests (95% CIs) will be two-

sided at a significance level of 0.05, and calculate the corresponding 95% confidence interval (CI). A statistical outlier is defined as a value that is inconsistent with other values and is clinically unreliable. Removal of outliers from analyses requires a thorough justification based on statistical and clinical background. Any outliers are to be reviewed during the blinded EDM (see Section 9.5). All statistical analyses will use SAS 9.4 version or above.

### **9.2.1 Demographic characteristics of subjects**

Age (years), sex, ethnicity, height (cm), body weight (kg), waist circumference (cm), and BMI ( $\text{kg/m}^2$ ). Descriptive statistical method is used to list the demographic data, including distribution of analysis sets of subjects, listings of datasets of subjects, subjects who violate the protocol and their reasons.

The demographic characteristics and other baseline characteristics are analyzed descriptively based on FAS. Continuous variables are described by number of subjects, mean, standard deviation, median, lower quartile (Q1), upper quartile (Q3), minimum and maximum, and calculate frequency number and frequency of counting and grading data.

### **9.2.2 Compliance and statistical analysis of concomitant medication**

Compliance is defined in Section 6.4.

Compliance is analyzed based on FAS. Concomitant medication is described in detail in a tabular format.

## **9.3 Planned safety analysis**

Safety endpoints are summarized using descriptive statistics based on SS. The number, number of subjects and incidences of various AEs and adverse reactions (including all AEs, TEAE/TRAЕ, AEs/adverse reactions of special interest, AEs/adverse reactions related to hypoglycemic events, AEs/adverse reactions of Grade III or above, SAEs/serious adverse reactions, AEs/adverse reactions leading to dose suspension, AEs/adverse reactions leading to study withdrawal) are summarized.

AEs are coded according to the Medical Dictionary for Regulatory Activities (MedDRA®). AE data listings, including preferred term (PT), system organ class (SOC), treatment, severity, and relationship to investigational drug s. The number of subjects with AEs and number of AEs are summarized by SOC and PT. AEs are summarized by severity and relationship to investigational drugs.

Laboratory evaluations, vital sign assessments, and ECG parameters are summarized at protocol-specified collection time points. Changes from baseline are summarized at each

protocol-specified time point. Changes of each clinical assessment parameter in clinical significance from baseline were cross-tabulated at each visit.

Concomitant medications are listed by subject, coded using the World Health Organization Drug Dictionary (WHODrug), and summarized by ATC.

### **Immunogenicity analysis:**

The proportion of ADA-positive subjects and NAb-positive subjects in each group are summarized, and listings of ADA-positive subjects and NAb-positive subjects are provided. Samples from positive subjects will be further investigated in vitro if necessary, and additional detailed analysis reports of ADA and NAb will be provided separately.

## **9.4 Scheduled efficacy analysis**

hypothesis-testing:

|                        |                                                                                   |
|------------------------|-----------------------------------------------------------------------------------|
|                        | Percentage change in body weight from baseline to W30 (one-sided $\alpha=0.025$ ) |
| Null hypothesis        | $H_0: \mu_T - \mu_C \geq 0$                                                       |
| Alternative hypothesis | $H_1: \mu_T - \mu_C < 0$                                                          |

$\mu_T$  is the mean percentage change of body weight from baseline in the first to fifth dose groups after 30 weeks of GZR18 treatment ( $\mu_T$  includes  $\mu_{T1}$ ,  $\mu_{T2}$ ,  $\mu_{T3}$ ,  $\mu_{T4}$  and  $\mu_{T5}$ , which corresponds to GZR18 s.c. 12 mg once every two weeks, GZR18 s.c. 18 mg once every two weeks, GZR18 s.c. 24 mg once every two weeks, GZR18 s.c. 48 mg once every two weeks and GZR18 s.c. 24 mg once-weekly respectively),  $\mu_C$  is the mean percentage change of body weight from baseline in the first to fifth dose groups after 30 weeks of placebo treatment.  $\alpha$  is significance level (Type I error rate).

Based on FAS, conduct effectiveness analysis on efficacy indicators. PPS as a supportive analysis result.

Primary endpoint analysis: the percentage of body weight change (%) from baseline at week 30 will be taken as the primary endpoint, which will be analyzed based on the covariance model (ANCOVA), where, with baseline body weight as the covariate and group as the fixed effect, and the change from baseline is the dependent variable. The following indicators will be then calculated: the least-squares mean (LSMean) and its two-sided 95% CI of the percentage of the change from baseline in both groups, as well as the LSMean difference between the treatment and control groups and its two-sided 95% CI.

Secondary endpoint analysis: The continuity variables will be analyzed by the same method as the primary endpoint analysis. The number of cases reaching the target end point

and the rate of reaching the target and its two-sided 95% CI will be counted in the analysis of the proportion between the two groups. At the same time, the rate difference between the two groups (the investigational drug group and the placebo group) and its two-sided 95% CI will be calculated. The rate of reaching the target and the two-sided 95% CI of the rate difference between the two groups will be calculated by the Clopper-Pearson Exact method.

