|  | 
which at least includes the start date, end date, severity, relationship with the investigational drug, outcome, duration and other information.
 
Safety variables (vital signs, laboratory data, ECG, etc.) will be grouped and summarized according to the time points specified in the protocol. Concomitant medications will be classified and summarized by group. All other safety data (physical examination, blood pregnancy, PHQ-9 score, etc.) will be reflected in the form of a list. The changes of laboratory examination results, ECG and physical examination before and after treatment will be statistically described in the form of a cross table, and the list of subjects with abnormal clinical significance after treatment will be listed.
 
The summarized table will present the number and percentage of events. In addition, the Treatment Emergent Adverse Events (TEAEs) will be summarized according to the severity and the relationship with the investigational drug. TEAE is defined as adverse events after the use of investigational drugs, and the analysis of adverse events will be based on TEAE. Serious adverse events will also be summarized and listed separately.
 
For the same subject, if an adverse event occurs multiple times, it will be counted as one case when calculating the incidence of adverse events.
 
The adverse events leading to the early termination of the study medication will be described.
 
Immunogenicity evaluation index: the titer of ADA and NAB in serum according to groups, and the number and incidence of subjects with positive ADA and NAB will be described.
 
Heart rate, blood amylase and lipase will also be further analyzed using the covariance model (ANCOVA).
 
The dose-dependent assessment of safety and tolerability is based on five GZR18 injection study groups with four dose groups and two administration methods, and compared with the placebo control group to summarize the adverse events in each group.
 
PK analysis
 
Based on PKPs, Phoenix WinNonlin 8.3 or above is used for PK analysis. The list and descriptive statistics of the investigational drugs are carried out, and the average drug concentration-time curves of individual and group are drawn respectively. The PK parameters are calculated by non atrioventricular model according to the actual blood sampling time, and the parameters are summarized by descriptive statistics. The main pharmacokinetic parameters are summarized by the number of subjects, arithmetic mean, standard deviation, coefficient of variation (CV),
 |

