##### **Secondary endpoints:**

##### **Efficacy endpoints**

- Proportion of subjects who achieved (yes/no) body weight reduction  $\geq 5\%$ , 10%, 15%, 20% from baseline.
- The changes from baseline in body weight, waist circumference, waist to hip ratio (waist/hip circumference), and BMI.
- The percentage change from baseline in body weight (%) after drug withdrawal at the last safe follow-up (W33).
- The changes from baseline in glucose metabolism indicators: HbA1c, FPG, fasting insulin, HOMA-IR and HOMA- $\beta$ .
- The changes from baseline in cardiovascular disease risk factors: blood pressure (systolic and diastolic blood pressure), pulse, TC, LDL-C, HDL-C, and TG.
- The changes from baseline in the impact of weight on quality of life score reported by patients: the total and individual scores of the IWQOL-Lite-CT, the total and individual scores of the physical and psychological parts of SF-36 scoring table.

---

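### Read literally, Section 9.4 adjusts secondary endpoints other than body weight for baseline body weight, not for their own baseline, which costs precision

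*Protocol*

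**What the plan says.** Section 9.4 describes the primary model as ANCOVA "with baseline body weight as the covariate and group as the fixed effect, and the change from baseline is the dependent variable". For the secondary endpoints the rule is a single sentence: "The continuity variables will be analyzed by the same method as the primary endpoint analysis". The statistical part of the synopsis (Section 1.1) repeats both statements.

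Section 3.2 lists the endpoints to which this sentence applies. They include "The changes from baseline in glucose metabolism indicators: HbA1c, FPG, fasting insulin, HOMA-IR" and HOMA-beta; blood pressure with "pulse, TC, LDL-C, HDL-C, and TG"; waist circumference, waist-to-hip ratio and BMI; and the IWQOL-Lite-CT and SF-36 scores. The list also holds change in body weight and percentage weight change at W33.

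The synopsis defines baseline as the last non-missing value before first dosing. The flowchart in Section 1.2 schedules each of these measures at screening, at W0 or at both, so every endpoint has a baseline value of its own.

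**The concern.** In an ANCOVA of change from baseline, the covariate that normally matters most is the baseline of the variable being analysed. In the primary model, baseline body weight is that variable. Carried over unchanged to insulin or systolic pressure, it is a different quantity, and the analysis becomes close to a plain comparison of change scores.

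Two things are at stake. The comparisons are less precise than the same data allow. They also respond to chance differences between groups in the endpoint's own baseline, which can be sizeable with 13 placebo subjects per dose group.

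These endpoints answer the stated secondary objective on glucose metabolism, cardiovascular risk factors and quality of life. For HbA1c, fasting glucose and insulin, the flowchart has only screening and W30 values, and the MMRM in Section 9.4 is a sensitivity analysis of the main efficacy indicators only. This ANCOVA is therefore the only between-group comparison the protocol states for them.

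**Working it through.** **The plan's own figures.** There is none to reproduce. Section 9.8 gives an effect, SD and power for the primary endpoint alone. No secondary endpoint has a stated effect, SD, correlation or power, so every correlation below is an assumption shown over a range.

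**Step 1: loss from the covariate.** Let the endpoint have the same variance s² at baseline and at W30, with correlation rho, and let body weight be unrelated to it.

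- Residual variance of change without own baseline: 2s²(1 − rho).
- Residual variance with own baseline as covariate: s²(1 − rho²).
- Ratio: 2(1 − rho)/(1 − rho²) = 2/(1 + rho), whatever the group sizes.

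The confidence interval widens by the square root of the ratio. The data are worth (1 + rho)/2 of what own-baseline adjustment would yield. The last column takes an own-baseline analysis with 80% power at one-sided 0.025 and computes Φ[(1.960 + 0.842)/√ratio − 1.960].

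| rho (assumed) | Variance ratio | CI width ratio | Information kept | Power, if 80% with own baseline |
|---|---|---|---|---|
| 0.3 | 2/1.3 = 1.54 | 1.24 | 65% | 62% |
| 0.5 | 2/1.5 = 1.33 | 1.15 | 75% | 68% |
| 0.7 | 2/1.7 = 1.18 | 1.08 | 85% | 73% |
| 0.9 | 2/1.9 = 1.05 | 1.03 | 95% | 78% |

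**Step 2: if body weight is not uninformative.** Suppose weight correlates r with the endpoint's baseline and predicts W30 only through it. The ratio becomes [2(1 − rho) − (1 − rho)²r²]/(1 − rho²). With r = 0.3:

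- rho 0.3: (1.4 − 0.49 × 0.09)/0.91 = 1.49
- rho 0.5: (1.0 − 0.25 × 0.09)/0.75 = 1.30
- rho 0.7: (0.6 − 0.09 × 0.09)/0.51 = 1.16
- rho 0.9: (0.2 − 0.01 × 0.09)/0.19 = 1.05

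A modest link with weight hardly changes the result. As r approaches 1 the ratio approaches 1, so the loss should be smaller for BMI and waist circumference than for laboratory values or questionnaire scores.

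**Step 3: chance imbalance.** The SE of the baseline difference, in SD units, is √(1/52 + 1/13) = 0.31 for one dose group against its own placebo subjects. Against the pooled placebo subjects (5 × 13 = 65) it is √(1/52 + 1/65) = 0.19. An analysis of change without own baseline turns a fraction (1 − rho) of any such imbalance into apparent treatment difference. For a one-SE imbalance against 13 placebo subjects that is 0.22, 0.16, 0.09 and 0.03 SD at rho 0.3, 0.5, 0.7 and 0.9.

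**Step 4: validity.** Randomisation makes the baseline difference zero on average, so the estimate is unbiased. In simulation of the weight-adjusted change model (log-normal outcomes, log-SD 0.4 to 0.8, rho 0.5 and 0.7, 52 active against 13 or 65 placebo, 2,000 null runs per setting), the one-sided type I error was 1.8% to 2.9% against a nominal 2.5%.

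**The case against.** The best defence is that baseline body weight is the own baseline of the primary endpoint. The same method can then be read as ANCOVA with group and the matching baseline, with details left to the SAP. That reading is possible and may be what was intended. But the protocol does not leave the covariate open: it names body weight and extends the method without qualification. If the matching baseline was meant, the same phrase settles it.

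It is also fair that these endpoints are unpowered secondaries in a phase II trial, and that at rho near 0.9 the loss is trivial. Both points limit the weight of the finding but do not remove it.

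A reader might infer more than the text supports:

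- **That all continuous secondary endpoints are affected.** They are not. For change in body weight and percentage weight change at W33, baseline body weight is the right covariate.
- **That skewed measures such as insulin, HOMA or triglycerides will be analysed untransformed.** The endpoints are defined as changes from baseline, but Section 9.4 says nothing on transformation, which is commonly left to the SAP. The screening limits on triglycerides and fasting glucose also shorten those tails at entry.
- **That much power is lost.** Large losses require a low correlation or marked skewness. The protocol gives no information on either.
- **That amylase and lipase are covered.** They are safety variables under a separate synopsis sentence, which names ANCOVA but no covariate and does not refer to the primary method.

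**Conclusion.** The point holds as a specification flaw. Taken at its word, Section 9.4 puts baseline body weight into models where the endpoint's own baseline belongs, for the continuous secondary endpoints other than body-weight change. The cost is precision: variance 1.05 to 1.54 times as large over assumed correlations of 0.9 down to 0.3, with equal variances and an uninformative body weight. Which end of that range applies to which endpoint cannot be told from the protocol. Exposure to chance baseline imbalance comes with it and is greatest if a dose group is compared with its own 13 placebo subjects. There is no bias in expectation, no inflation of type I error and no effect on the primary analysis.

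**What to change.** In Section 9.4 and the matching synopsis text, replace the reference to the primary method with a statement that each continuous secondary efficacy endpoint is analysed by ANCOVA of change from baseline, with group as fixed effect and the baseline value of that same endpoint as covariate. Keep baseline body weight for the body-weight endpoints. Make the change before unblinding.

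The cost is wording and a model statement per endpoint. No new data are needed and there is no statistical downside. Log-scale analysis of skewed laboratory measures can be considered in the SAP; it is optional and not part of this point, and it would change the summary measure from the changes defined in Section 3.2.
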